## Abstract

**Background:**

Research has almost exclusively focused on the neck in order to explain the mechanisms of persistent pain after motor vehicle collisions (MVC). However, studies have shown that low back pain after MVC is as common as neck pain. Also, posttraumatic stress disorder (PTSD) is common after MVCs, and evidence indicate that PTSD may be linked to the development of pain and disability. PTSD has even been proposed as “the missing link” for some in the development of chronic low back pain. Unfortunately, PTSD often goes unattended in low back pain rehabilitation and very few randomized controlled studies exists targeting both conditions. Hence, the aim of the present study is to investigate the potential additional effect of the trauma therapy “Somatic Experiencing®” (SE) in addition to physiotherapy (PT) compared to PT alone for patients with chronic low back pain and comorbid PTSD.

**Methods:**

The study is a two-group randomized controlled clinical trial in which participants (*n* = 140) are recruited consecutively from a large Danish spine center in the Region of Southern Denmark, between January 2016 and December 2017. Patients are randomly allocated to one of the two conditions: SE + PT or PT alone. Measurements of effect are carried out at baseline before randomization, post-intervention, 6 and 12 months post-randomization. The primary outcome is a 20% reduction in disability (Rolland Morris Disability Questionnaire) at 6 months post-randomization. Secondary outcomes are: PTSD symptoms, pain intensity, pain-catastrophizing, fear of movement, anxiety and depression.

**Discussion:**

Comorbid PTSD is currently not targeted in back pain rehabilitation although highly prevalent. If the SE intervention shows to have an additional effect on disability and pain, the study is likely to have a positive impact on the management of chronic low back pain and will have immediate clinical applicability.

**Trial registration:**

Current Controlled Trials Registration August 4, 2017: NCT03244046. Retrospectively registered.

## Background

For decades, research has almost exclusively focused on the neck in order to explain the mechanisms of persistent pain after motor vehicle collisions [1]. Indeed, neck pain is common after motor vehicle collisions (MVC). However, large-scale cohort studies have shown that low back pain (LBP) is as common as neck pain with a prevalence of 37% six weeks after a MVC [2, 3]. Also, wide spread pain across body regions are found to account for almost twice as much of pain related disability (60% vs. 34%) as neck pain alone [2]. Moreover, low back pain is also common after sexual assaults [4, 5]. Finally, collision-related characteristics have consistently shown to be poor predictors of pain and disability after minor MVCs [6–8]. Together, these findings indicate that neurobiological changes related to the psychological stress response to the traumatic event may be important mechanisms in the understanding of low back pain. Indeed, psychological distress such as PTSD is common after MVCs and studies find that comorbid PTSD in chronic pain is associated with a more severe symptom profile with respect to disability, pain and psychological distress [6, 9–11]. PTSD has even been proposed as “the missing link” for some individuals in the development of chronic low back pain [10].

The mutual maintenance model [12] and the shared vulnerability model [13] outlines how elevated levels of arousal, attention bias, anxiety sensitivity, catastrophic thinking and avoidance behaviors are mechanisms maintaining both PTSD and pain. Moreover, examining effect modifiers of exercise rehabilitation programs for chronic whiplash, it is indicated that patients with comorbid PTSD respond less well compared to patients without PTSD. Together, these results indicate that a combined treatment of psychotherapy and exercises may be optimal treating comorbid pain and PTSD [14].

Unfortunately, PTSD often goes unattended in low back pain rehabilitation and very few randomized controlled studies exists targeting both conditions. To our knowledge three randomized controlled trials (RCT) exist targeting comorbid PTSD and pain [15–17] and only one has investigated somatic experiencing® (SE) as a method in a mixed trauma population with chronic low back pain [15]. The other two studies are cognitive behavioral therapy (CBT) trials for motor vehicle-related PTSD. Andersen and colleagues [15] found that a brief SE intervention (6–12 sessions) + treatment-as-usual (TAU: 4–12 sessions of supervised exercises for low back pain) significantly reduced PTSD symptoms and fear of movement (kinesiophobia) compared to TAU alone (*n* = 91). However, no additional effect was achieved in relation to disability and pain compared to TAU alone. Beck and colleagues [16] compared group CBT with a minimal contact comparison condition (*n* = 44) and found a moderate reduction in PTSD symptoms for the CBT group. However, change in pain severity was not different from the controls. The second CBT trial was a pilot study (*n* = 26) on whiplash-associated disorders assessing the effect of trauma-focused CBT compared to a waiting list. Opposite, the other studies, a moderate reduction was found in both neck related disability, pain and PTSD compared to the waiting list [17]. However, the results should be interpreted with caution, given the small sample size and no active control condition applied. Also, only change in PTSD symptoms was considered a clinically important effect [17]. In conclusion, it seems that both SE and CBT approached in the context of chronic pain have an effect on PTSD symptoms. However, given the different nature of the previous studies and the lack of a proper control condition, the effect of targeting PTSD symptoms in comorbid low back pain still remains inconclusive with respect to the effect on pain and disability. More studies with sufficient statistical power and a homogeneous trauma population and a proper control condition are needed. In particular, SE needs to be further assessed given that only two RCTs of SE exists [15, 18] and only the study by Andersen and colleagues testing SE in the context of pain rehabilitation.

SE differs from trauma-focused CBT in its focus on interoception and musculoskeletal sensations rather than exposure to traumatic memories and experiences [19–21]. In SE, traumatic memories are targeted indirectly by gradually developing an increasing tolerance for unpleasant sensations and emotions. For these reasons SE resembles techniques applied in mindfulness and acceptance and commitment therapy for chronic pain [22], where training in sustained attention to unpleasant sensations such as pain or difficult emotions are means to stay mindful in the present moment and thereby facilitate new interoceptive experiences that contradict those of overwhelming anxiety and helplessness associated with pain or traumatic experiences [23].

Theoretically, SE may target important mechanisms as described in the mutual maintenance model [12] and the shared vulnerability model [13]. Indeed, the limited evidence indicate that SE is effective for PTSD and perhaps for fear of movement [15] which according to the mutual maintenance model is one of the mechanisms mutually maintaining pain and PTSD. However, results remain inconclusive in relation to pain and pain related disability. The study by Andersen and colleagues [15] has a number of limitations that may explain the lack of an effect on pain and disability. First of all, the brief SE intervention (mean number of sessions = 6) may not have been sufficient. Also, the mixed trauma population with PTSD dating more than 10 years back in time may have limited the effect. Finally, the long follow-up time 12-months post-randomization may also have deflated the results. For these reasons SE still needs to be investigated as a method in a more homogeneous trauma population with comorbid pain and PTSD and with more sessions of SE. Hence, the aim of the current study is to test whether somatic experiencing® (SE) targeting PTSD related to unresolved accident and injury related trauma in combination with supervised exercises for low back pain would reduce pain-related disability.

First, we hypothesize that an additional SE intervention will reduce pain-related disability compared to physiotherapy alone at 6 months follow-up. Secondly, compared to physiotherapy alone, we hypothesize that the additional SE intervention will reduce all secondary outcomes at 6 months follow-up (PTSD, pain, pain-catastrophizing, fear of movement, anxiety, and depression.

## Methods

### Study design and participants

The study is a two-group randomized controlled clinical trial in which participants (*n* = 140) are recruited consecutively from a large Danish spine center in the Region of Southern Denmark, between January 2016 and December 2017 with follow-up post-intervention, 6 and 12 months post-randomization. Ethics approval was obtained from the local science ethics committee (trial number S-20150136) and all participants gave written informed consent before study entry. Figure 1 illustrates the patient flow in this study. Based on an earlier study in the spine center it is estimated that about 10% will suffer from possible PTSD/sub-clinical PTSD [24]. Of approximately 5000 eligible patients, 500 are expected to have experienced a traumatic event (DSM-IV criteria A [25]) and to screen positive for possible PTSD/sub-clinical PTSD. Of those it is expected that a minimum of 40% will volunteer to participate in the study. In total, 140 patients will be randomized to SE (*n* = 70) and to PT (*n* = 70).

**Fig. 1 Fig1:**
[figure not shown]
Flow Diagram of the Trial

All patient in the spine center are referred for spinal pain and have the right to be referred to the Spine Centre if their improvements has not been satisfactory in primary care. Before study entry, all participants will give written informed consent. Department personnel perform multidisciplinary assessments of patients with spinal pain after referral from general practitioners. A standardized clinical examination and use of magnetic resonance imaging (MRI) are central elements. The clinical examination includes spine movement tests, Lasegue’s test, patellar and Achilles reflexes etc. In addition to the standard screening procedure at the spine center, all patients that have been exposed to traffic accidents or injuries are screened for possible PTSD.

Patients are considered eligible for inclusion if they have low back pain and within 5 years of time has been involved in a MVC or an injury and meet the criteria for possible sub-clinical or clinical PTSD (see procedures below) as measured on the Harvard Trauma Questionnaire part IV [26], are between 18 and 70 years of age, proficient in written and spoken Danish. Exclusion criteria are known psychiatric comorbid diseases such as bipolar depression, psychosis or other serious psychiatric diseases. Also, drug dependence or other ongoing psychotherapeutic interventions will lead to exclusion.

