### Secondary outcomes

PTSD symptoms are measured using the Harvard Trauma Questionnaire part IV [26]. The Harvard Trauma Questionnaire consists of 17 items with a 4-point Likert scale (1 = not at all to 4 = very often). The 17 items relate to PTSD’s core clusters: avoidance (7 items), re-experiencing (5 items), and hyperarousal (5 items). An item is deemed to be positively endorsed if scores are ≥3. The Harvard Trauma Questionnaire follows the diagnostic criteria for the PTSD diagnosis according to the DSM-IV. In the current study, a possible PTSD diagnosis is proposed if participants report at least one re-experiencing symptom, three avoidance symptoms, and two hyperarousal symptoms. Possible sub-clinical PTSD is proposed in cases where the patients either miss one symptom of avoidance or hyperarousal. The Harvard Trauma Questionnaire self-report measure of PTSD has previously been reported as having an 88% concordance with interview-based estimates of PTSD [26].

Pain intensity is measured as the average score of three 11-point Likert scales measuring peak pain intensity, average pain intensity over the past 2 weeks as well as current pain intensity [30]. Each scale measures pain intensity on a 0–10 numerical rating scale (NRS: [31]) with 0 defined as no pain and 10 as the worst imaginable pain.

The Pain Catastrophizing Scale [32] is used to measure catastrophic thinking related to pain. The PCS ask participants to reflect on past painful experiences, and to indicate the degree to which they experienced each of 13 thoughts or feelings when experiencing pain, on a 5-point Likert scale with (0 = not at all, 4 = all the time). A scale sum score is calculated from all items, with a high score indicating a high level of pain catastrophizing.

Fear of re-injury due to movement is measured with the Tampa Scale for Kinesiophobia (TSK: [33]). TSK is a 17-item scale assessing fear of movement on a 4-point Likert scale ranging from 17 to 68 with higher scores indicating higher levels of kinesiophobia. The scale is commonly used in diverse chronic pain samples and has good construct and predictive validity [34, 35].

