## Discussion

The primary aim of the present study is to investigate the potential additional effect of a SE intervention in addition to physiotherapy (PT) compared to PT alone for patients with chronic low back pain and comorbid PTSD. The intervention is expected to have an additional positive effect on both disability and all secondary outcomes compared to PT alone. Also, as indicated by earlier preliminary results in whiplash, the comorbid presence of PTSD seems to prevent a good response to physiotherapy [14]. For these reasons, it is believed that an effective treatment of PTSD combined with supervised exercises for low back pain will have an additional effect on both disability and pain. Although Andersen and colleagues [15] only found SE to have a significant effect on PTSD symptoms and fear of movement (kinesiophobia), a number of limitations by the study makes it impossible to draw definite conclusions about the possible additional effect of SE on disability and pain. First of all, the SE intervention was very brief and the trauma symptoms were severely chronic dating back decades. Also, a more structured physiotherapeutic program needs to be tested in combination with a full-length SE program.

The study addresses a prevalent problem, chronic low back pain. Comorbid PTSD is currently not targeted in back pain rehabilitation although highly prevalent after back pain related to injuries. If the SE intervention shows to have an additional effect in disability and pain, the study is likely to have a positive impact on the management of chronic low back pain and will have immediate clinical applicability.

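### The aim is stated for patients with PTSD, but the trial enrols possible clinical or sub-clinical PTSD, so the pooled primary estimate needs the wider label

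*Protocol article*

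**What the plan says.** **Aim.** The Discussion gives the primary aim as the additional effect of an "SE intervention in addition to physiotherapy (PT) compared to PT alone for patients with chronic low back pain and comorbid PTSD". The Abstract (Background) names the same population. The Background section argues that SE should now be studied in a "more homogeneous trauma population with comorbid pain and PTSD and with more sessions of SE". None of these places mentions sub-clinical PTSD.

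**Entry rule.** Under Study design and participants, patients with low back pain and a recent collision or injury are eligible if they "meet the criteria for possible sub-clinical or clinical PTSD (see procedures below) as measured on the Harvard Trauma Questionnaire part IV".

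**Definitions.** Under Secondary outcomes, possible PTSD requires "at least one re-experiencing symptom, three avoidance symptoms, and two hyperarousal symptoms" on a self-report questionnaire. For the lower category, "Possible sub-clinical PTSD is proposed in cases where the patients either miss one symptom of avoidance or hyperarousal".

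**Recruitment.** Study design and participants counts the two categories together: "it is estimated that about 10% will suffer from possible PTSD/sub-clinical PTSD". No split is given.

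**Analysis.** The Statistics section plans intention-to-treat mixed models with gender and age as covariates in all of them. Randomization is in permuted blocks of six. PTSD level is mentioned in neither place.

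**The concern.** The primary question is framed for people with PTSD, while the people who will answer it include an unknown proportion who do not meet the protocol's own symptom rule for possible PTSD. The intention-to-treat contrast averages over both categories. If the report keeps the wording of the aim, a positive result would be read as evidence in PTSD and a null result as evidence against benefit in PTSD. The pooled estimate alone supports neither statement.

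The label matters here because PTSD carries the argument. The Discussion reasons that PTSD stands in the way of a good response to physiotherapy and that treating it should therefore improve disability. The Background names the mixed trauma population of the earlier SE trial as one possible reason why that trial found no effect on disability. The new trial narrows the type and recency of the trauma but leaves PTSD level mixed.

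**Working it through.** **1. Aim and entry rule side by side**

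| Place in the protocol article | Population |
|---|---|
| Abstract, Background | chronic low back pain with comorbid PTSD |
| Discussion, first paragraph | the same |
| Study design and participants, recruitment estimate | possible PTSD and sub-clinical PTSD together |
| Study design and participants, eligibility | possible sub-clinical or clinical PTSD |
| Secondary outcomes | defines each category separately |

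The full rule needs at least 1 + 3 + 2 = 6 endorsed symptoms in the set pattern. One avoidance symptom short gives a minimum of 1 + 2 + 2 = 5, and one hyperarousal symptom short gives 1 + 3 + 1 = 5. Sub-clinical patients are therefore below the protocol's threshold by definition, though close to it.

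**2. Recruitment figures**

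5000 × 0.10 = 500 screen-positive patients, and 500 × 0.40 = 200 expected volunteers for 140 places. Both figures cover the two categories together. The sub-clinical share cannot be recovered from the document.

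**3. The stated sample size**

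The 140 cannot be rebuilt from the protocol's own inputs. No SD is given, and the 20% is not identified as relative or as percentage points. Working backwards with two-sided alpha 0.05 and 80% power:

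- n per arm = 2 × (1.96 + 0.84)² / d². With d = 0.50 this rounds up to 63.
- 2 × 63 = 126, and 126 / 0.90 = 140.
- Power with 63 per arm at d = 0.50 is 0.801.

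So 140 is consistent with a standardized difference of 0.50. That value is an assumption and is not in the document.

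**4. What a smaller effect in sub-clinical patients would do**

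All inputs are assumed: d = 0.50 in patients meeting the full rule, a sub-clinical share s, and a relative effect f in the sub-clinical group. The pooled effect is 0.50 × [(1 − s) + s × f]. Power is approximately Φ(pooled effect × √(63/2) − 1.96).

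| f | Pooled effect, s = 20% | Power | Pooled effect, s = 50% | Power |
|---|---|---|---|---|
| 1 | 0.500 | 0.80 | 0.500 | 0.80 |
| 0.75 | 0.475 | 0.76 | 0.4375 | 0.69 |
| 0.5 | 0.450 | 0.71 | 0.375 | 0.56 |
| 0 | 0.400 | 0.61 | 0.250 | 0.29 |

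The document supports no particular row. With f = 1 nothing is lost, whatever the share.

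**5. Precision of an estimate in patients meeting the full rule**

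With 63 evaluable per arm and s from 20% to 50%, about 50 down to 32 per arm meet the full rule. The 95% half-width is 1.96 × √(2/n):

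- n = 50: 0.39 SD
- n = 32: 0.49 SD

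**6. An interaction test**

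With f = 0.5 the effects differ by 0.25 SD. The standard error is √[2/(63(1 − s)) + 2/(63s)]:

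- s = 50%: √(2/31.5 + 2/31.5) = 0.36, power about 11%
- s = 20%: √(2/50.4 + 2/12.6) = 0.45, power about 9%

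Such a test could not tell dilution from absence of benefit.

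**The case against.** The strongest reply is that nobody reading the Methods could mistake who is enrolled. The recruitment estimate, the eligibility rule and the questionnaire definitions all use the wider category openly and consistently. The narrower phrase is a short label in the Abstract and Discussion of a condensed article, and the aim at the end of the Background sets no full-PTSD threshold. Both categories are only possible diagnoses from a self-report screen, and a difference of one symptom is not a sharp clinical boundary. Admitting near-threshold patients is a legitimate pragmatic choice. A subgroup estimate or a severity covariate may also sit in an analysis plan that is not shown.

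Most of this stands. There are not two competing entry rules, and the choice to enrol both categories is not a flaw. The mismatch between aim and entry rule remains, however, and both are protocol content. The two analysis suggestions are support for the relabelling and are not omissions to be held against the article.

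A reader might go further and infer that sub-clinical patients dilute the effect, so that the trial is underpowered and its 80% is wrong. The documents do not support that:

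- The share, the relative effect and the 0.50 SD are all assumptions.
- The recruitment estimate draws the 140 patients from both categories together, and nothing ties the 20% target to full PTSD.
- The whiplash finding behind the rationale compares patients with PTSD to patients without it. It says nothing about patients one symptom short.

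**Conclusion.** The point holds as one of population and interpretation. The stated aim is narrower than the enrolled population, and no limit is set on the share who miss the protocol's own rule for possible PTSD. The primary estimate is a valid randomized contrast in possible clinical or sub-clinical PTSD as screened by questionnaire. It should not be reported as an effect in patients with PTSD.

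The size of the mismatch is unknown because no split between the categories is given. The effect on power runs from none, with equal benefit, to substantial under the more extreme assumed combinations. It is a conditional possibility, not an error in the stated 80%. The relabelling is warranted even if dilution is zero.

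**What to change.** 1. In the aim, and later in the conclusion, describe the population as possible clinical or sub-clinical PTSD on the Harvard Trauma Questionnaire.
2. State in the Statistics section that the sample size and its 80% power refer to this pooled population.
3. Report the number of patients in each category by arm.
4. Add baseline PTSD status, already recorded at screening, to gender and age in the models.
5. Pre-specify a descriptive supportive estimate: the 6-month RMDQ difference with its confidence interval in patients meeting the full rule under Secondary outcomes. Place no reliance on an interaction test.

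If an unseen analysis plan already contains items 4 and 5, only the wording changes and the counts are needed.

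The cost is some wording, one covariate and one extra estimate on data already collected. The population label becomes less sharp, and the supportive estimate will be too imprecise to settle the question in patients meeting the full rule. Eligibility, sample size and data collection stay as they are.

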### Randomization and masking

Patients are randomized by random permuted blocks of six. Randomizations are consecutively numbered in sealed opaque envelopes and administered by a project nurse, blinded to treatment assignments. Patients are randomly allocated to one of the two conditions: Somatic Experiencing® (SE) + physiotherapy (PT) or PT alone. Treatment is initiated within 2 weeks after randomization. Measurements of effect are carried out at baseline before randomization, post-intervention, 6 and 12 months post-randomization. The study statistician will be blinded to treatment allocation.

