### The somatic experiencing® intervention

In the SE intervention, patients receive up to 12 sessions of 1 h SE therapy delivered by a certified SE therapists (a physiotherapist or a pain nurse) with several years of experience in SE and pain management. The SE intervention follows the nine-step model as outlined by Peter Levine [21] and involves gradually eliciting awareness of body sensations associated with the traumatic event. By the process of ‘titration’, patients are gradually encouraged to access, feelings and body sensations as means to restore equilibrium to the autonomic nervous system and thereby alleviate hyperarousal, re-experiencing and avoidance of trauma-related experiences and thoughts. Fewer than 6 sessions are considered as non-compliance.

The overall allowable time frame for the interventions is 16 weeks. The expected timeframe for the final treatment and post-intervention assessment is 12–14 weeks for the SE + physiotherapy group and 8–10 weeks for the group only receiving physiotherapy. An overview of the program is outlined in Table 1.

**Table 1 Tab1:** Overview of the SE Intervention

Steps	Theme	Therapeutic approach
1	Create a safe environment	To facilitate a therapeutic environment that promotes a feeling of security. Build a therapeutic relationship with the patient. The therapist assumes an accepting stance.
2	Support initial exploration of sensations	To support a mindful approach to the exploration of bodily sensations. Facilitate the experience of positive sensations.
3	Pendulation	By the process of “pendulation” to encourage the patient to come in contact with bodily sensations. To help the client experience how the body alternates between pleasant and unpleasant sensations. By facilitating this awareness, the patient learns how to relax.
4	Restore active defensive responses	To help the patient to restore active defensive responses that has “collapsed” because of the overwhelming nature of the trauma. Support impulses to active responses, including defensive orienting, fight and flight.
5	Titration	Because the central nervous system cannot distinguish between the original trauma and being overwhelmed by the re-experience of the traumatic event in therapy, the aim is to help the patient to gradually move in and out of the trauma. This by ensuring a continuous grounding in the body with attention to the bodily responses while moving into and out of the content of the traumatic event.

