### Outcome measures

All outcomes are obtained by an investigator blinded to group allocation at baseline, post-intervention, and at follow-up at 6 and 12 months post-randomization. The outcomes are as follows:

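### One fixed block size of six, in a single-centre trial where treatment is visible, leaves up to a quarter of allocations deducible by a fully informed observer

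*Protocol article*

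**What the plan says.** All references are to the protocol article.

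- **Allocation rule** (Randomization and masking): "Patients are randomized by random permuted blocks of six". One block size is given and no stratification factor is named.
- **Concealment** (same section): "Randomizations are consecutively numbered in sealed opaque envelopes and administered by a project nurse, blinded to treatment assignments".
- **Setting and ratio** (Study design and participants): patients are "recruited consecutively from a large Danish spine center in the Region of Southern Denmark", and 140 are to be split 70 and 70.
- **Arms**: "Patients are randomly allocated to one of the two conditions: Somatic Experiencing® (SE) + physiotherapy (PT) or PT alone". Under Procedures, all participants receive physiotherapy. Under The somatic experiencing intervention, one arm also receives up to 12 one-hour sessions from a certified SE therapist.
- **Who is blinded**: the project nurse who administers the envelopes, the study statistician and the outcome investigator ("All outcomes are obtained by an investigator blinded to group allocation at baseline, post-intervention, and at follow-up at 6 and 12 months post-randomization"). Nothing says that patients or therapists are blinded, and with these arms they could not be.
- **Order of events**: consent comes before study entry, baseline measurement before randomisation, and treatment starts within 2 weeks after it.

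**The concern.** In a 1:1 block of constant size six, once three patients have gone to one arm, the rest of the block must go to the other. Numbered opaque envelopes give no protection against this, because nothing has to be opened. The SE arm is recognisable from the treatment given, and one unstratified sequence at one centre is the easiest kind to follow.

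At stake is allocation concealment. A person who expects a particular arm next can delay or bring forward an invitation or an entry. The plan leaves some room for this. It expects 500 patients to screen positive and at least 40% of them to volunteer (500 × 0.40 = 200), for 140 places. Some exclusions, such as serious psychiatric disease, call for judgement. The covariates named under Statistics are gender and age, which would not reliably correct for selection on other prognostic factors.

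**Working it through.** The article gives no predictability figure, so there is none to reproduce. The inputs are block size 6 (Randomization and masking), and ratio 1:1, N = 140 and one centre (Study design and participants).

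**Step 1: exact enumeration of one block.** A block with three patients per arm has C(6,3) = 20 equally likely orders. The next allocation is certain when one arm is already used up.

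- Position 4 is certain if the first three are alike: 2/20 = 0.10.
- Position 5 is certain if the first four hold three of one arm: 2 × C(4,3)/20 = 8/20 = 0.40.
- Position 6 is always certain.

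The best guess is the arm with fewer patients so far in the block, or a coin toss when the arms are level.

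| Position | P(already certain) | P(best guess correct) |
|---|---|---|
| 1 | 0 | 0.50 |
| 2 | 0 | 3/5 = 0.60 |
| 3 | 0 | 0.6 × 0.5 + 0.4 × 3/4 = 0.60 |
| 4 | 0.10 | 0.1 × 1 + 0.9 × 2/3 = 0.70 |
| 5 | 0.40 | 0.4 × 1 + 0.6 × 0.5 = 0.70 |
| 6 | 1.00 | 1.00 |
| Sum | 1.50 | 4.10 |

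Certain share: 1.5/6 = 25%. The closed form agrees: a block of 2m has 2m/(m + 1) certain allocations, and with m = 3 that is 6/4 = 1.5. Best-guess rate: 4.1/6 = 68.3%, against 50% with no information.

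**Step 2: the whole trial.** 140 patients make 23 full blocks (138 patients) plus 2, and the last two add no certain allocation.

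- Certain: 23 × 1.5 = 34.5, and 34.5/140 = 24.6%.
- Best guess: (23 × 4.1 + 0.5 + 0.6)/140 = 95.4/140 = 68.1%.

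**Step 3: varying block sizes.** This is a simulation of 1,000 trials of 140 patients. The assumed observer knows the set of sizes (equally likely) but not their order, and updates after every allocation.

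| Block sizes | Certain | Best guess correct |
|---|---|---|
| 6 only | 24.6% | 68.1% |
| 4, 6 | 5.5% | 69.2% |
| 4, 6, 8 | 2.2% | 68.0% |
| 6, 8, 10 | 1.6% | 66.3% |

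The first row matches the exact result. With 4, 6 and 8, about 0.0216 × 140 = 3 allocations are certain instead of 34.5. The best-guess rate hardly moves.

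**The case against.** The strongest reply is that the 25% needs an observer the article does not describe. That person must know or infer the block size, know where blocks start, have every earlier allocation in order, and be able to influence enrolment. The article does not say that recruiting staff see allocations. Delivering physiotherapy does not reveal the arm, since everyone receives it. Treatment starts are also a delayed signal. If accrual is even, 140 patients over 24 months (about 104 weeks) is 1.35 a week, so up to 2 × 1.35 = 2.7 patients, nearly half a block, may be randomised but not yet visibly treated. Recruitment is consecutive, all patients exposed to accidents or injuries are screened, and PTSD eligibility rests on a questionnaire threshold. Consent and baseline already come first. All of this stands. It makes 25% an upper bound and narrows the opportunity, but does not close it: deduction can still affect whom to invite and when.

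It is also fair that who prepared the list, and whether staff knew the block size, may be settled in the full protocol. Those silences are not faulted here. The constant block size is stated, and that is the point.

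A reader might also infer that the nurse who administers the envelopes cannot be blinded. The text does not support that. It does not say who opens them, and the phrase can mean unaware until opening, or handing them over unopened. At most the sentence could be made clearer.

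**Conclusion.** The point holds as a weakness in allocation concealment that is cheap to reduce. A constant block of six at 1:1 makes 25% of allocations in a full block certain, or 34.5 expected among 140, for an observer with full knowledge. Anyone with less knowledge can be certain of fewer. The figure rests on a single sequence (stratification is not mentioned, so its absence is inferred) and on the SE arm being visible, which follows from the interventions although the article does not use the term open-label.

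Two stronger readings should be resisted. One is that a quarter of the allocations were foreseen or that the comparison is biased; the document reports no foreknowledge. The other is that this compounds the self-reporting of disability by patients who know their treatment; that is a separate source of bias, unaffected by block size.

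**What to change.** For patients still to be randomised:

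1. Have someone outside the clinic prepare a new list with randomly varying block sizes, for example 4, 6 and 8, and do not disclose the sizes to recruiting staff. Start it when the current block of six is complete.
2. Keep the running record of allocations from those who invite and enrol. Varying the blocks removes most of the certainty but leaves the best-guess rate near 68%, so the first step is not enough alone.

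Opening envelopes only after consent and baseline needs no change; it is in substance the stated order.

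**Cost.** A new list and set of envelopes, and a slightly larger possible imbalance at the end. With fixed sixes, 140 patients end with two in an open block, so the arms differ by at most 2. With blocks up to 8, they could differ by 4.

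**Reach.** Only patients not yet randomised benefit, and the article does not say how many remain. Recruitment was planned from January 2016 to December 2017 and registration is dated August 2017. If the change were made about then, with even accrual, it would cover roughly 5 of 24 months: 140 × 5/24, about 29 patients. If none remain, what is left is to report the block size and whether recruiting staff knew it.
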